***7.2 Intrapartum data***

7.2.1 Maternal variables, including oxytocin requirements, artificial membrane rupture, dosage of labor analgesia, duration of labor, episiotomy, mode of delivery, maximal temperature, estimated blood loss, volume of oral intake and volume of intravenous fluid.

7.2.2 Pain severity is assessed using the Numeric Rating Scale (NRS, an 11-point scale where 0 indicated no pain and 10 indicated the most severe pain) before analgesia, at 10 and 30 minutes after analgesia, and at full cervical dilation.

7.3.3 Calculate data, including total fluid intake (oral and intravenous) and calories supplied by oral and intravenous fluid.

***7.3 Postpartum data***

7.3.1 Neonatal variables, including gender, birth weight, Apgar scores at 1 and 5 minutes after birth, and neonatal ward admission. Neonatal blood glucose level is tested instantly after birth using a blood glucose monitor (Accu-Chek®, Roche, Germany), and will be retested every 30 minutes when necessary.

7.3.2 Maternal blood glucose level is tested instantly after giving birth using a blood glucose monitor (Accu-Chek®, Roche, Germany) and will be retested every 30 minutes when necessary.

**8. Outcome assessment**

***8.1 Primary outcomes***

The rate of cesarean delivery.

***8.2 Secondary outcomes***

8.2.1 Duration of labor.

8.2.2 Rate of forceps delivery.

8.2.3 The NRS score of hunger/thirst.

8.2.4 Maternal blood glucose after giving birth.

8.2.5 1- and 5-minute Apgar scores.

8.2.6 The umbilical artery pH value after birth.

8.2.7 Neonatal blood glucose after birth.

8.2.8 The rate of neonatal ward admission.

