***4.2 Sample size calculation***

In a pilot trial of our own, the rate of cesarean delivery was 8% of parturients with carbohydrate drink and 12% of those with clear liquid drink. We assumed similar rates in the present study. With the significance level set at 0.05 (two-sided) and power set at 80%, the sample size required to detect difference was 1760 parturients. Considering a drop-out rate of about 10%, we plan to enroll 2000 parturients. Sample size calculation was performed with the Stata 10.0 software (Stata Corp. LP, College Station, TX, USA).

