**6. Interventional protocol**

***6.1 Epidural labor analgesia management***

6.1.1 As a routine practice, cervical dilatation is assessed at 4-hour intervals after delivery room admission. Epidural labor analgesia is initiated when the cervix was dilated to 1 cm or more.

6.1.2 Before the implement of analgesia, an intravenous line is established with Ringer’s lactate solution (50 ml/h; Na^+^ 130 mmol/L, K^+^ 4 mmol/L, 0.009 kcal/ml).

6.1.3 After confirming the position of the epidural catheter inserted between L2-3 or L3-4 intervertebral space, a 10 ml mixture of 0.1% ropivacaine (AstraZeneca AB, Södertälje, Sweden) plus 0.5 μg/ml sufentanil (EuroCept BV, Ankeveen, Netherlands) is administered as a loading dose; an additional 5 ml mixture is administered 10 minutes later if the numeric rating scale (NRS, an 11-point scale where 0=no pain and 10=the worst pain) of pain remained ≥4.

6.1.4 An intermittent epidural bolus pump (ZZB-II; Jiangsu Aipeng Medical Science and Technology Company Ltd., Nantong, China) is attached 30 minutes later, which is established with 200 ml mixture of 0.07% ropivacaine plus 0.45 μg/ml sufentanil and programmed to deliver 6-ml boluses with a lockout interval of 20 minutes and a background infusion of 4 ml/h. The maximal dose limit is 26 ml/h.

6.1.5 The PCEA pump is stopped at the end of the third stage of labor.

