***6.2 Study intervention***

6.2.1 Study intervention will be administered during epidural labor analgesia.

6.2.2 Parturients in the carbohydrate-rich group are provided with an oral carbohydrate-rich solution [Outfast®: 285 mOsm/kg, 14.1% carbohydrate (maltodextrin 100g/L, fructose 23.9g/L, glucose 16.9g/L), Na^+^ 2.0 mmol/L, K^+^ 4.9 mmol/L, 0.58 kcal/ml; Yichang Humanwell Pharmaceutical Co, Ltd, Hubei, China] and are advised to drink as will during labor.

6.2.3 Parturients in the low-carbohydrate group are advised to drink commercially available low-carbohydrate beverages as will (Pocarisweat®: 0.26 kcal/ml, Otsuka Pharmaceutical Co. Ltd, Tokyo, Japan; Gatorade®, 0.24 kcal/ml, PepsiCo, Chicago, IL, USA; or Mizone®: 0.21 kcal/ml, Danone, Guangzhou, Guangdong, China).

6.2.4 All participants have free access to water, but solid foods are not permitted.

6.2.5 Dietary intake prior to labor analgesia and after the third stage of labor are not interfered.

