***13.5 Intrapartum variables***

Numeric variables will be analyzed using the independent-samples t test or Mann-Whitney U test; categorical variables will be analyzed using the chi square test, continuity correction chi square test or Fisher exact test. Missing data will not be replaced.

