***13.6 Efficacy evaluation***

13.6.1 Primary endpoint:

13.6.1.1 The incidence of cesarean delivery will be calculated. Comparation between groups will be performed using Chi-Square test, with difference between groups expressed as relative risk (95% CI). The upper limit of the 95% CI of less than 1 is regarded as statistical superiority.

13.6.1.2 The interactions between treatment effect and predefined factors will be assessed separately with logistic regression models. The predefined factors include study site, age, body mass index, prepartum anemia, medical comorbidity, obstetric disease, and gynecological disease. The relative risk (and 95% CI) for each subgroup and the P values of treat-by-covariate interactions will be displayed in a forest plot.

13.6.2 Secondary endpoints:

13.6.2.1 Categorial variables (rate of forceps delivery, the rate of neonatal ward admission) between groups will be compared using Chi-Square test, continuity correction Chi-Square test, or Fisher’s exact test. Missing data will not be replaced.

13.6.2.2 Numerical variables (maternal and neonatal blood glucose after giving birth, 1- and 5-minute Apgar scores and the umbilical artery pH value) between groups will be compared using independent sample t-test or Mann-Whitney u test. Missing data will not be replaced.

13.6.2.3 Ranked data (NRS score of hunger/thirst) will be compared using Mann-Whitney u test. Missing data will not be replaced.

13.6.2.4 Relative risk (95% CI) for categorial variables, mean/median difference (95% CI) for numerical variables/ranked data will be calculated.

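### Duration of labor has no stated clock start; if it runs from labor onset, the unadjusted test in 13.5 may give away precision to time before the drink began

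*Protocol*

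**What the plan says.** Section 8.2 gives the outcome as "8.2.1 Duration of labor" and nothing more. Section 7.2 collects it among the intrapartum variables ("dosage of labor analgesia, duration of labor, episiotomy, mode of delivery"), again without a start or end point.

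The treatment window is narrower than labor. Section 6.2.1 states: "Study intervention will be administered during epidural labor analgesia". Section 6.1.1 sets when that window can open: "Epidural labor analgesia is initiated when the cervix was dilated to 1 cm or more". Section 6.2.5 leaves earlier intake alone: "Dietary intake prior to labor analgesia and after the third stage of labor are not interfered".

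For the analysis, section 13.5 states: "Numeric variables will be analyzed using the independent-samples t test or Mann-Whitney U test". Section 13.6.2.2 names the numeric secondary endpoints, "Numerical variables (maternal and neonatal blood glucose after giving birth, 1- and 5-minute Apgar scores and the umbilical artery pH value", and duration of labor is not among them, so 13.5 is the only place that supplies its test. Section 13.4.2 adds adjustment for baseline variables found imbalanced. The prepartum list in 7.1 contains neither the time of labor onset nor the time from onset to analgesia.

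**The concern.** Labor duration is usually counted from labor onset. On that reading each woman's value is the sum of two parts: time before analgesia, when neither arm has the study beverage, and time after it, when the drink can act. The first part carries no treatment signal. Unless it is negatively related to the second part, it adds variance, and the interval for the first-listed secondary outcome is wider than it need be. A real shortening of labor after the drink starts would then be harder to see.

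The protocol uses initiation of analgesia as the anchor for baseline hunger, thirst and glucose (7.1.3, 7.1.4) and for the adverse event window (9.1). It gives duration of labor, which depends directly on its time origin, no such anchor.

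How women delivered by cesarean enter the duration analysis is a separate question and is not addressed here.

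**Working it through.** **The plan's own figure.** The only sizing in the protocol is for cesarean delivery (4.2): "the rate of cesarean delivery was 8% of parturients with carbohydrate drink and 12% of those with clear liquid drink", two-sided 0.05, 80% power. With the unpooled variance formula, n per arm = (1.960 + 0.842)² × (0.12×0.88 + 0.08×0.92) / 0.04² = 880 after rounding up, or 1760 in total, as stated. Allowing 10% drop-out gives 1760/0.9 = 1956, so 2000 is sufficient. The protocol gives no mean, standard deviation or effect for labor duration, so everything below rests on assumptions.

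**Set-up.** Let Y be time from analgesia to birth, P time from labor onset to analgesia, and T = P + Y. Scale so that SD(Y) = 1, and write r = SD(P)/SD(Y) and ρ = corr(P, Y). The drink is assumed to act on Y only.

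- Variance of T: 1 + r² + 2rρ.
- Variance of Y: 1.
- T is noisier than Y only if r² + 2rρ > 0, that is, if ρ > −r/2.

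**Power of the unadjusted comparison of T.** Choose the effect that gives 80% power on Y. At 880 per arm this is 2.802 × √(2/880) = 0.1336 SD. By the normal approximation, power on T is Φ(2.802/SD(T) − 1.960). Sample size cancels, so 1000 per arm gives the same results.

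| r | ρ = −0.5 | ρ = −0.25 | ρ = 0 | ρ = +0.25 |
|---|---|---|---|---|
| 0.25 | 87.5% | 82.5% | 77.6% | 72.9% |
| 0.5 | 89.9% | 80.0% | 70.7% | 62.8% |
| 0.75 | 87.5% | 72.9% | 61.1% | 52.1% |
| 1 | 80.0% | 62.8% | 50.8% | 42.5% |

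For example, at r = 1 and ρ = 0, SD(T) = √2 = 1.414, and 2.802/1.414 − 1.960 = 0.021, so power is 50.8%. At r = 0.5 and ρ = −0.25, SD(T) = √(1 + 0.25 − 0.25) = 1, and nothing is lost.

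**Adjusting for P.** In a linear model on the hours scale, T and Y differ by P exactly. With P as a covariate, the estimated arm effect is therefore the same whichever clock is used. The residual variance is 1 − ρ² in both cases.

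- Against unadjusted T: (1 + r² + 2rρ) − (1 − ρ²) = (r + ρ)², never negative.
- Against unadjusted Y: 1 − (1 − ρ²) = ρ², never negative.

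At r = 1 and ρ = 0, the variance of T halves, from 2 to 1. At r = 0.5 and ρ = −0.25, it falls from 1.00 to 0.94. At r = 0.5 and ρ = −0.5, it stays at 0.75. On the power scale above, the adjusted analysis gives 80.0% at ρ = 0, 82.5% at ρ = ±0.25 and 89.9% at ρ = ±0.5, whatever r is.

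**The case against.** The strongest reply is that the protocol never says pre-epidural hours are counted. That is correct: 8.2.1 and 7.2 are silent, and counting from labor onset is the ordinary reading of the term, not protocol text. An analysis plan or case report form not shown here may define the clock. If so, the definitional half of this point is already met. The choice of test in 13.5 remains, and adjustment helps, or at worst does no harm, under either clock.

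The second reply is that the direction of the effect is not established. This also stands. Analgesia is given on request and divides one labor into two parts. A later start, at greater dilatation, may leave less labor to come, which would make ρ negative. A reader might infer that the comparison necessarily loses power, or that epidural-to-birth time should simply replace total duration. The protocol supports neither: when ρ ≤ −r/2, total duration is no less precise than epidural-to-birth time and may be more so.

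Third, a reader might infer that a chance difference in pre-epidural hours would be mistaken for a drink effect. If allocation does not influence when analgesia starts, such a difference is sampling error and the confidence interval already reflects it.

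The rule in 13.4.2 is only partial cover. It acts on listed baseline variables found imbalanced, and pre-analgesia time is not listed.

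Finally, the protocol does not say whether randomization comes before or after analgesia starts, and allocation is not masked (5.2). If randomization comes first, pre-analgesia time could be affected by allocation. This limits the remedy and is carried into the fix.

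**Conclusion.** The point holds in a limited form. The outcome has no stated time origin. On its ordinary meaning it includes time before treatment, and the stated test makes no use of that time. The consequence is a possible loss of precision in a secondary outcome for which the trial was not powered. The primary comparison is untouched.

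The size cannot be derived from the protocol. Under an assumed r of 0.25 to 1 and ρ = 0, 80% power on post-epidural time becomes 77.6% to 50.8% on total duration. Positive correlation makes this worse, and ρ ≤ −r/2 removes it. What does not depend on these unknowns is that, in a linear model and in large samples, adjusting for pre-analgesia time is at least as precise as either unadjusted comparison. That result assumes that pre-analgesia time is unaffected by allocation. Severity is minor to moderate.

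**What to change.** 1. In 8.2.1, state when the clock starts and stops.
2. In 13.5 or 13.6.2, name duration of labor and compare it by a regression, or a rank-based equivalent, adjusted for time from labor onset to initiation of analgesia.
3. Report epidural-to-birth time alongside the adjusted total duration, not in place of it.
4. Add the times of labor onset and of initiation of analgesia to the recorded data, since 7.1 does not list them.
5. In section 5 or 6, state whether randomization precedes or follows initiation of analgesia, so that the covariate's status as pre-treatment can be judged.

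The cost is a few lines of text and two recorded times. Total duration stays the reported quantity, so comparability with other reports of labor duration is kept. The adjustment relies on open-label allocation not influencing when analgesia starts. If randomization comes first, that should be stated as an assumption, and pre-analgesia time tabulated by arm. The precision result is exact for a linear model on the hours scale and only a guide for rank-based methods.

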**7. Data collection**

***7.1 Prepartum data***

7.1.1 Demographic data, including gender, date of birth, and body mass index.

7.1.2 Diagnosis and medical history, including duration of gestation, gravidity, prepartum comorbidities, comorbid obstetric disease, medical treatment, history of allergy to food and drugs, and prepartum hemoglobin

7.1.3 Subjective discomfort (degree of hunger and thirst) is assessed using the Numeric Rating Scale (NRS, an 11-point scale where 0 indicated no hunger/thirst and 10 indicated the most severe hunger/thirst) at the initiation of epidural labor analgesia.

7.1.4 Maternal blood glucose level is tested using a blood glucose monitor (Accu-Chek®, Roche, Germany) at the initiation of epidural labor analgesia.

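### Hunger/thirst and umbilical artery pH are tested as secondary outcomes, but section 7 schedules hunger/thirst only at baseline and does not list pH

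*Protocol*

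**What the plan says.** Protocol section 8.2 lists eight secondary outcomes. Two of them are "8.2.3 The NRS score of hunger/thirst", which carries no assessment time, and "8.2.6 The umbilical artery pH value after birth". Section 13.6.2.3 assigns the hunger/thirst score a Mann-Whitney test between groups. Section 13.6.2.2 assigns pH a t test or Mann-Whitney test. Both clauses say that missing data are not replaced.

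The measurements are set out in section 7:

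- **Prepartum (7.1.3).** "Subjective discomfort (degree of hunger and thirst) is assessed using the Numeric Rating Scale", with the time fixed in the same sentence: "10 indicated the most severe hunger/thirst) at the initiation of epidural labor analgesia".
- **Intrapartum (7.2.2).** "Pain severity is assessed using the Numeric Rating Scale", before analgesia, at 10 and 30 minutes after it, and at full dilation. Hunger and thirst are not mentioned.
- **Postpartum (7.3).** The neonatal item reads "7.3.1 Neonatal variables, including gender, birth weight, Apgar scores at 1 and 5 minutes after birth, and neonatal ward admission", followed by neonatal blood glucose. The maternal item is blood glucose only.

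On the timing of treatment, section 6.2.1 says: "Study intervention will be administered during epidural labor analgesia". Section 5.2 names hunger and thirst among the measures taken by assessors outside perinatal care, but gives no time.

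**The concern.** An outcome needs a measurement taken after the treatment can have acted. For hunger/thirst, the one scheduled score is taken as the drinks are about to start. A site that follows section 7 to the letter hands the analyst a baseline score and nothing later, and the analyst cannot recover a later score that nobody was told to take. A test on that score would compare the arms before exposure, and a null result could be reported as the drink having no effect on hunger or thirst. These are outcomes on which a drink could plausibly act directly.

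For pH the problem is of another kind. The outcome needs a specimen taken at birth. With no collection item, the protocol does not say which births are sampled or how, nor whether all nine centres do it. As missing values are not replaced, the comparison would rest on whichever newborns happened to have a result.

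**Working it through.** No calculation bears on this point. The check is to match each outcome in 8.2 to an item in section 7 that is recorded after the drink starts.

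| Secondary outcome | Item after the drink starts | Baseline item |
| --- | --- | --- |
| 8.2.1 Labor duration | 7.2.1 | – |
| 8.2.2 Forceps delivery | 7.2.1 (mode of delivery) | – |
| 8.2.3 Hunger/thirst NRS | **none** | 7.1.3 |
| 8.2.4 Maternal glucose | 7.3.2 | 7.1.4 |
| 8.2.5 Apgar scores | 7.3.1 | – |
| 8.2.6 Umbilical artery pH | **none** | – |
| 8.2.7 Neonatal glucose | 7.3.1 | – |
| 8.2.8 Neonatal ward admission | 7.3.1 | – |

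Six of eight outcomes have a matching item and two do not.

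**Is the 7.1.3 score a baseline score?** It is filed under prepartum data and timed at the start of analgesia. The drinks are given during analgesia (6.2.1), so the score precedes or coincides with the start of exposure.

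**Is the gap an omission or a drafting style?** Maternal glucose is the natural comparison. It is scheduled at the start of analgesia (7.1.4) and again after birth (7.3.2), and its outcome is labelled as the value after birth (8.2.4). Hunger/thirst has the first half of that pair and lacks the second. Likewise, every other neonatal outcome is in 7.3.1 and pH alone is not.

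**Does the analysis section resolve it?** No. Section 13.4.2 compares the arms on all baseline variables and adjusts all analyses for any found imbalanced. As the schedule stands, the 7.1.3 score falls under that rule and is also the only value available for the test in 13.6.2.3.

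**Is anything else affected?** No. The primary outcome, caesarean delivery, is covered by mode of delivery in 7.2.1. The sample size depends only on the caesarean rates and reproduces. For 8% versus 12%, two-sided 0.05 and 80% power, n per arm = (1.960 + 0.842)² × (0.08 × 0.92 + 0.12 × 0.88) / 0.04² = 7.849 × 0.1792 / 0.0016 ≈ 879.1. This rounds up to 880, or 1760 in total, as section 4.2 states.

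**The case against.** The best defence is that the protocol, read as a whole, shows what was meant. Section 5.2 has independent assessors recording hunger and thirst, so an outcome score was intended. Section 13.4.2 handles baseline variables by standardized differences, while 13.6.2.3 places the hunger/thirst test under secondary endpoints, which suggests two separate scores. The lists in 7.2.1 and 7.3.1 are introduced as non-exhaustive. Section 8.2.6 itself names the specimen and says it is taken after birth. The case report form is not shown and may collect more.

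Much of this stands, and it limits the point. A reader might infer that the two outcomes cannot be obtained, or that no pH value would exist for any of the roughly 2000 women. The text does not establish that; it shows only that section 7 schedules neither measurement. A reader might also infer that the expected hunger/thirst difference is exactly zero by randomisation. That would need a score taken before allocation is known, in all randomised women. The protocol does not say when allocation is disclosed relative to the score. The trial is open label, the score is self-reported, and section 3.4 removes some women after randomisation. Finally, a reader might suppose that pH would be available only for a clinically selected group of births. No passage describes cord sampling practice at any centre.

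What the defence does not supply is a time. Section 5.2 says who scores hunger and thirst, not when, and an open-ended list is not an instruction that nine centres can follow uniformly. A statistical analysis plan can say which value is analysed, but it cannot schedule a measurement that the protocol leaves out.

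**Conclusion.** The point holds as an inconsistency between the outcome and analysis sections on one side and the data collection section on the other. It affects two of eight secondary outcomes. If the schedule is followed as written, the only hunger/thirst value available for 13.6.2.3 is a baseline score that cannot show an effect of the drink. Umbilical artery pH has a planned test but no stated sampling or coverage. The conclusion concerns the written plan and is not evidence that the data were never gathered. It rests on reading 7.1.3 as the sole hunger/thirst item, which the text of section 7 supports. It should be corrected, but it does not threaten the main conclusion of the trial, because the primary outcome and sample size are unaffected.

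**What to change.** **Hunger/thirst.** Add to 7.2 a post-intervention hunger and thirst NRS score at a stated time that also captures women delivered by caesarean. One option is to take it with the pain NRS at full cervical dilation, or at the decision for caesarean if that comes earlier. State in 8.2.3 and 13.6.2.3 that this score is the outcome and that the 7.1.3 score is its baseline. The cost is one extra 0–10 rating each for hunger and thirst, at a point where pain is often being scored already. There is a small drawback: a time tied to the course of labor means that women are scored after differing lengths of exposure, and labor duration and caesarean delivery are themselves outcomes. Any stated post-intervention time that covers all women would meet the need.

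**Umbilical artery pH.** Reconcile 7.3.1 with 8.2.6. If the centres already sample cord blood at every birth, list pH in 7.3.1, which adds only a data item. If they do not, sampling about 2000 births at nine centres would be an added procedure rather than one more line on the form. In that case, remove pH from the formally tested secondary outcomes in 8.2.6 and 13.6.2.2, and report it descriptively with the number of births sampled in each arm.

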**9. Adverse events and management**

***9.1 Definition***

An adverse event indicates any unpredictable, unfavorable medical event that is associated with any medical intervention and occurred during the study period. It can be related to the study beverage administration or not. It can manifest as any uncomfortable signs (including abnormal laboratory findings), symptoms or transient morbidity. In the present study, adverse events are monitored from the initiating of epidural labor analgesia until 2 hours postpartum in the delivery room (before being transferred to the postpartum ward).

